## Abstract

**Background:**

Neonatal mortality is a major health burden in Bungoma County with the rate estimated at 31 per 1000 live births and is above the national average of 22 per 1000. Nonetheless, out of the nine sub county hospitals, only two are fairly equipped with necessary infrastructure and skilled personnel to manage neonatal complications such as prematurity, neonatal sepsis, neonatal jaundice, birth asphyxia and respiratory distress syndrome. Additionally, with more than 50% of neonates delivered without skilled attendance, in below par hygiene environments such as home and on the roadsides, with non-existent community based referral system, the situation is made worse. The study aims to evaluate the progress made by an intervention “Collaborative Newborn Support Project” geared towards reducing neonatal mortality rate by 30% between October 2015 and December 2018 in Bungoma County, Kenya.

**Methods/Design:**

This intervention will take a quasi-experimental design approach with experimental and control sites. The project will involve pre- and post-intervention data collection with comparison group to assess intervention effects. The primary outcome will be the percentage reduction of neonatal mortality in Bungoma County. Secondary outcomes include; a) Percentage of mothers or care givers able to identify at least three danger signs in neonates in the project area, b) Proportion of neonates with complications referred to specialized neonatal centers, through the call center, c) Percentage of health providers in neonatal care units who adhere to expected neonatal standards of care (rapid and complete application of standard protocols), d) Percentage increase in neonates with severe complications in the specialized neonatal units and e) Percentage of neonates who stay in neonatal care units beyond 5 days.

**Discussion:**

We outline implementation details of the ongoing ‘Collaborative Newborn Support Project’ in Bungoma County, Kenya. This includes strategies in the operations of the telehealth platform, call centre service, community engagement and measuring of the outputs and outcomes. The funding and ethical approvals have been obtained and the study commenced.

**Trial registration:**

PACTR201712002802638 Retrospectively registered on 5th December 2017 at Pan African Clinical Trials Registry.

**Electronic supplementary material:**

The online version of this article (10.1186/s12913-018-3293-5) contains supplementary material, which is available to authorized users.

## Background

Approximately 2.7 million new-borns die each year accounting to 43% of deaths of children under 5 years [1]. Maternal and new-born deaths were the focus of millennium development goals 4 and 5 which were not met by 2015 and are currently captured in the sustainable development goals [2, 3]. Kenya has a big neonatal mortality burden currently at 22 out of 1000 live births with Bungoma County at 31 per 1000 live births [4]. Major contributors to the morbidity and mortality challenge include poor new-born health coverage, low levels of perinatal care [5], adverse cultural practices including unskilled home deliveries, poor cord care comprising application of cow dung, lizard excreta, herbs and mud to ‘facilitate’ cord healing and early weaning. Additionally, the continuum of care from antenatal care to delivery and postnatal care and new-born health, is highly disjointed in most rural districts due to inadequate capacities (infrastructural, personnel and supplies) and strategies worsening the situation [6–8].

A key pillar in supporting strategies to mitigate new-born morbidity and mortality is improvement of quality of care. Even though there is no clear definition of new-born quality of care, important elements include; skilled care during pregnancy and delivery encompassing skilled birth attendance, emergency obstetric care for maternal and new-born complications and post-natal care for mothers and babies [9, 10]. In defining quality of care in regards to maternal health, Hulton et al.*,* [11] point to effective and timely access to services. The WHO has published a comprehensive quality of care guideline titled ‘Standards for improving quality of maternal and newborn care in health facilities’ that aims to set the bar especially for the developing world [12]. Kenya has developed its own quality strategy called ‘The Kenya Quality Health Model’ that strives to guide different sectors of health provision including maternal and newborn on attaining International Standards Organisation certification. Nonetheless, the model does not cover process implementation but provides tools for continuous quality improvement, the Plan-Do –Check- Act cycle et cetera [13]. The quality of care guidelines will of necessity be live to the different emerging strategies in increasing access to quality care especially in peripheral or poor resource settings factoring diverse metrics in their evaluation [14]. These include mobile and telehealth applications, call centre services and other technologies.

The collaborative new-born support was conceived to address the unacceptably high new-born morbidity and mortality rates in Bungoma County with the purpose of enhancing survival of neonates, improve quality of care and accessibility of new-born care services in the nine sub-counties of Bungoma.

### Anticipated impact

The project will contribute towards the two outcomes with activities linking as follows; 1. Increased access to and utilisation of quality neonatal health services since new-born special care units in 7 sub county hospitals will be set-up, introducing these services to the sub counties, establishing a mobile phone based follow up system for neonates will empower mothers to make timely health seeking decisions and avert complications. The community sensitization sessions will inform the members and stakeholders on availability of the services stimulating demand.

Secondly, the project will contribute to health system management strengthening to deliver quality neonatal health services because 90 medical staff will be trained, mentored and supported through a tele-health platform by paediatricians from Kenya Paediatric Association and Mount Kenya University. It is anticipated that this strategy will build the healthcare workers confidence in neonatal care and create a pool of trainers in the rural facilities. Moreover, repackaging and distributing 1000 copies of best practice neonatal clinical guidelines to facilities in the county will provide quick reference. A community referral system for neonatal health services will be enhanced working with community based midwives. Besides, it is anticipated that mothers and particularly with pre-natal challenges will choose to deliver in these facilities for better neonatal outcomes, raising skilled attendant deliveries.

### Hypothesis

Quality neonatal care, call centre service, tele-health and community engagement will reduce new-born morbidity and mortality in Bungoma county, Kenya

### Study questions

To what extent does increase in community knowledge on neonatal complications and availability of quality services affect mothers/new born caregivers utilization of hospital services in Bungoma County?Will improved quality of neonatal care lead to an increase in utilization of new born care services in Bungoma County?Does improved information flow amongst health practitioners result in better services for neonates in Bungoma County?

## Methods

### Study setting

Bungoma County (coordinates 0.8479° N, 34.7020° E), Western Kenya has a population of approximately 1.7 m and an area of 2069 km^2^. The County has an urbanization rate of 21.7%, literacy levels of 60.5% with 87.6% of residents between the ages of 15–18 attending primary school. It has a poverty rate of 52.9% and access to electricity access of 4.5% [4, 15]. The main ethnic groups in the county are the Bukusu and Sabaoti sub-tribes of Luhya and Kalenjin respectively.

The main economic activities include: Agriculture, manufacturing and retail services. Agriculture is the backbone of Bungoma County and most families rely on crop production and animal rearing. The main crops include maize, beans, finger millet, sweet potatoes, bananas, Irish potatoes and assorted vegetables. These are grown primarilly for subsistence with the excess sold to meet other family needs. On the other hand, the main cash crops include sugar cane, cotton, palm oil, coffee, sun flower and tobacco. Most families integrate livestock production with farming. The main livestock kept include cattle, sheep, goats, donkeys, pigs, poultry and bees. Most of this is on a small scale but some farmers also produce milk and poultry products for commercial use. Milk and sugarcane farmers sell their produce mainly through cooperative societies.

The County is comprised of 6 constituencies: Kimilili, Webuye East, Webuye West, Sirisia, Kanduyi, Bumula and Mt. Elgon. This guided the selection of project intervention sites. These sites are in the following facilities; Bungoma County referral hospital, Webuye Sub-County hospital, Kimilili, Sirisia, Bumula, Naitiri, Mt. Elgon, Sinoko and Chwele.

### Study design

This intervention will take a quasi-experimental design approach with an experimental and control site. The project will involve pre- and post-intervention data collection with one comparison group to assess intervention effects.

The study will be conducted at level 4 and 5 hospitals, each hospital having high volume of clients and covering a sub-county, all with similar maternal, newborn and child health indicators. Five hospitals will be the implementation sites while 4 hospitals will be control sites in a step wedge approach. The implementation sites will be selected purposely. The control sites will receive the full intervention after 1 year when the first set of comparison with the intervention site has been completed.

The 5 experimental site hospitals will receive a set of interventions which include: refurbishing of new born units, installation of equipment such as incubators, respirators, Ambu bags, and radiators. Establishment of a tele-health platform to enable free flow of information amongst clinicians and obstetricians, establishment of a call center for follow up of patients, training of health care providers in neonatology, and creating awareness amongst the community will be key cross cutting interventions, implying they will benefit the intervention site as well as control site. The control sites will not receive the main intervention benefits (equipped specialized newborn units) until after 1 year of implementation in the experimental sites.

The project will undertake a baseline, mid-term and end-line surveys. The step wedge design which allows for the measurement of process, outcome and impact indicators within each site (at different time points) will be used. The design also allows a comparison between different combinations of the intervention components.

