### Control group – Minimizing bias and contamination

To minimize bias and contamination, the intervention sites will be selected purposely from the nine county and sub- county hospitals. The sites selected will include the two facilities that have some level of neonatal facilities to ensure that the intervention sites and the control sites have distinct features separating the two.

We will measure the utilization of services in the selected facilities at baseline, mid-term and end-line levels.

To determine utilization of neonatal services, we will collect data directly from the source through a data abstraction form in the nine health facilities throughout the project period. Further, the community health workers and volunteers will also provide information of the number of cases they refer to specific facilities. Cases that fail to arrive at the health facilities will also be captured and the data from the facilities and the community health workers will be cleaned, cross checked and analyzed to provide required results for utilization of neonatal services.

Quality of care will be determined through observations of service provision by clinicians, as well as checking use of neonatal equipment and the severity of conditions managed by the health providers in the units.

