#### Selection of hospitals for the study

There are 177 health facilities in Bungoma County of which 12 are hospitals and the rest are health centers, dispensaries and clinics. In this study, nine high volume health facilities will be selected to participate in the study. Five Facilities will be intervention sites while four health facilities will be the control sites. The intervention sites will be selected purposely from the nine project facilities.

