#### Rationale

The project will establish 7 new special care units and enhance capacity in 2. Following the 3 months module based competency based neonatology course for 90 health care workers in these units, it will be important to provide medical consultation support by pediatricians. This will facilitate timely clinical decision making including and not limited to; judicious use of medicines such as antibiotics, change of treatment, fluids administration, nutritional calculations, immunization decisions, evolution of diagnosis, need for referral and follow up strategies. This virtual support will build the clinicians confidence in clinical management of newborns, knowing that they can ask and get help at any time of the day, all week, ultimately improving outcomes.A major challenge for clinicians working in peripheral, rural areas in Kenya, has been keeping in touch with best care practices due to inability to access this information, lack of continuous education on how to apply the updates on best care and failure of follow up on adoption of best care practices. The telehealth platform will provide virtual best care practices updates service regularly and interactively. Pediatricians and the special units’ clinicians will be able to discuss on implementation of the updates, challenges they face and lessons learnt. This will promote free flow of information between the consultants and the clinicians, promoting best care practices and newborn outcomes.The telehealth platform will enable data collection on clinical challenges and gaps that will inform project evaluation, areas of emphasis in the continuous medical education and enhanced efficiencies in other processes such as call center follow up and referral systems.

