#### Study assumption

The main assumption in this study is that the intervention and control sites have similar characteristics. Since the facilities are under different Health Facility Management Teams, and health priorities, and decisions made by the HFMT are dependent on the catchment community of each facility, there is a possibility that the intervention and control sites are not necessarily comparable. However, since the sites have low PNC coverage and similar challenges affecting access and utilization of neonatal health services, it is assumed that the differences will not affect the outcome of the study.

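### Three of the five first-year intervention hospitals are hand-picked from seven unequipped ones; this does not minimise bias, and the year-1 between-site comparison is left open to selection bias

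*Protocol article*

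**What the plan says.** All references are to the protocol article.

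- **Number of sites and timing.** Selection of hospitals for the study states that "nine high volume health facilities will be selected to participate in the study". Study design adds: "Five hospitals will be the implementation sites while 4 hospitals will be control sites in a step wedge approach". Controls receive the equipped newborn unit after one year, once a first comparison with the intervention sites is complete.
- **How the first step is filled.** Study design says "The implementation sites will be selected purposely", and Selection of hospitals for the study repeats that "The intervention sites will be selected purposely from the nine project facilities". No draw is described, and no criterion is given for ordering the unequipped hospitals. Study setting says that constituencies guided the choice of project sites, but it lists all nine facilities and does not order them.
- **The equipped hospitals.** The abstract's Background says that "out of the nine sub county hospitals, only two are fairly equipped with necessary infrastructure and skilled personnel". The section Control group – Minimizing bias and contamination says "The sites selected will include the two facilities that have some level of neonatal facilities". Read with the sentence before it, this places both in the intervention group. The Rationale for the telehealth platform confirms the split: "The project will establish 7 new special care units and enhance capacity in 2".
- **The justification.** That same control-group section gives the minimising of bias and contamination as the reason for purposive choice, and wants the two groups to differ visibly.
- **The assumption.** Study assumption takes the two groups to be alike, grants that "there is a possibility that the intervention and control sites are not necessarily comparable" because management teams and priorities differ, and then assumes that the differences will not matter.

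**The concern.** All seven unequipped hospitals eventually receive a unit, so only the order is open, and the project decides it. Choosing the order by judgement makes every assignment known and steerable in advance. It cannot reduce selection bias, and the article says the opposite. The article also asks for groups that are distinct in one section and assumes similar groups in another.

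The contrast at stake is the year-1 comparison between sites. Telehealth, the call centre, training and community awareness reach both groups, so this is the comparison that should isolate the equipped newborn unit. Any hospital feature that influenced the choice and also bears on the trend in deaths or utilisation would be read as an effect of the unit.

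**Working it through.** **1. Counts, all from the article.**

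- Hospitals: 5 intervention + 4 control = 9; 2 equipped + 7 unequipped = 9. The counts agree across sections.
- First-year places left after the two equipped hospitals: 5 − 2 = 3.
- Unequipped hospitals left as controls: 7 − 3 = 4.
- Possible ways to choose the three: C(7,3) = 35.

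**2. Which comparison is exposed.** Primary outcome measure compares deaths at all nine facilities during implementation with deaths at the same facilities in a similar earlier period. Which three hospitals go first creates no between-site bias in that measure. The year-1 intervention v control comparison in Study design does depend on it.

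**3. What baseline data remove.** The design collects data before and after in both groups. Comparing change from baseline cancels stable differences in level. It does not cancel differing trends, or regression to the mean if a site's recent results influenced its selection. The relevant spread is therefore that of the site-level change. The article gives no such figure, so the results below are in SD units.

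**4. Size under assumption.** Assume that the changes the seven sites would show without the unit are independent normals with SD 1, and that the three sites are picked on a judgement that correlates ρ with that change.

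- Expected normal order statistics for n = 7, top three: 1.352, 0.757, 0.353; sum 2.462.
- Gap at ρ = 1: 2.462/3 + 2.462/4 = 1.44 SD (simulation with 200,000 runs: 1.43).
- Gap at other values: ρ × 1.44.

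| ρ (assumed) | Expected 3 v 4 gap, SD of change |
|---|---|
| 0 (a draw) | 0 |
| 0.3 | 0.43 |
| 0.5 | 0.72 (simulation 0.71) |
| 0.8 | 1.15 |
| 1.0 | 1.44 |

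The sign is unknown, because the basis for the choice is not stated.

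**5. What a draw would and would not do.**

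- The expected 3 v 4 gap becomes 0, but chance imbalance remains: SD of the gap = √(1/3 + 1/4) = 0.76.
- Smallest exact permutation p-value: 1/35 = 0.029 one-sided, 2/35 = 0.057 two-sided.
- The full 5 v 4 contrast stays confounded by the two equipped hospitals. If they differ from the others by D, the residual bias is (2/5) × D, that is 0.2, 0.4 or 0.8 SD for assumed D of 0.5, 1 or 2 SD. A draw therefore protects the 3 v 4 contrast among the seven, not 5 v 4.

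**The case against.** The study is openly called quasi-experimental with a comparison group. It states purposive selection, concedes possible non-comparability and nowhere claims randomisation. It has also commenced, so a draw may no longer be possible. With only seven hospitals, chance imbalance after a draw has an expected absolute size of about 0.76 × √(2/π) = 0.61 SD, similar to the bias under moderate selection.

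Much of this stands. The label is honest, and the value of a draw lies in removing systematic bias and supporting a randomisation test, not in guaranteeing balance. But the label does not rescue the statement that hand-picking minimises bias, nor does it settle the clash between wanting distinct groups and assuming similar ones. Those are faults in the text as written.

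A reader might infer more than the documents support:

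- **That the headline mortality result is biased by the choice of sites.** It is not: the primary measure is before-after at all nine facilities.
- **That the spurious effect could rival the 30% target.** Multiplying 1.43 SD by assumed between-hospital coefficients of variation of 10%, 20% and 30% gives 14%, 29% and 43%. This takes a spread in levels, which baseline data largely cancel, and assumes perfect selection. The 30% target also belongs to the county-wide before-after measure, not to a contrast between sites.
- **That no valid test of the year-1 difference exists.** A controlled before-after test is available under parallel trends. What is missing is a test justified by randomisation.
- **That sites were chosen for keen management or after a bad year.** No such criterion appears. These are possibilities, not findings.

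**Conclusion.** The point holds for the year-1 between-site comparison only. Three of the five first-year places are filled by judgement from seven unequipped hospitals, no criterion is stated, and the claim that this minimises bias is wrong. The direction and size of any bias cannot be found from the documents. A correlation of 0.3 to 0.5 between the choice and the site-level change would give a gap of about 0.4 to 0.7 SD of that change. This rests on a normal model and assumed correlations, and it cannot be turned into a percentage of deaths without a between-hospital spread that the article does not report. It is worth correcting because this contrast carries the inference about the newborn units themselves.

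**What to change.** - **If the order is still open:** in Study design and Selection of hospitals for the study, replace purposive choice among the seven unequipped hospitals with a draw of three for the first step and four for the second. Test by permutation over the 35 allocations.
- **In any case:** make the 3 v 4 comparison of change from baseline among these seven the main year-1 between-site contrast. Report the two already-equipped hospitals separately. Delete the statement that purposive selection minimises bias, and reconcile the wish for distinct groups with Study assumption.
- **If no draw was made:** state the reason for choosing each site, and present the contrast as non-randomised and dependent on parallel trends.

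Cost: the wording changes are small, and the numbers of hospitals and units stay the same. With a draw, the project gives up choosing the order. Two of nine hospitals leave the main contrast. Chance imbalance remains (SD of the gap 0.76), and the exact test cannot fall below 0.029 one-sided or 0.057 two-sided, so the contrast is better reported as an estimate with its uncertainty than as a pass or fail at two-sided 5%.
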